### 3.5 Study Variables

#### 3.5.1 Dependent Variables

The primary outcome for this study is mental health literacy, and the secondary outcome is help-seeking behaviour. Both the primary and secondary outcomes will be measured at baseline, 2 weeks post-intervention and, 1 month follow-up.

#### 3.5.2 Independent Variable

The independent variable for this study is a health education intervention based on IMB theory delivered via website.

#### 3.5.3 Covariates

The covariates for this study are socio-demographic factors such as age, gender, ethnicity, and household income level.

### 3.6 Operational Definition

**Table 3.2 Operational Definition**

| Variable               | Operational Definition                                                                                                                                                                          |
|-------------------------------|--------------------------------------------------------------------------------------------------------------------------------------------------------------------------------------------------------|
| Gender                 | Gender will be categorized into male and female.                                                                                                                                                       |
| Ethnicity              | Ethnicity will be categorized into Malay, Chinese, Indian, Lain-lain                                                                                                                            |
| Household Income Level | Household income is combined income for all people sharing a particular household. It will be categorized according to <RM4360, >RM4360 – RM9619, and >RM9619.                                         |
| Mental Health Literacy | Mental Health Literacy will be assessed Mental Health Literacy Scale. It consists of 35 items. The items will be measured using 4-points and 5-points Likert scale. There are six attributes (based on |

---

|                              |                                                                                                                                                                                                                                                                                                                                                                                                              |
|------------------------------|--------------------------------------------------------------------------------------------------------------------------------------------------------------------------------------------------------------------------------------------------------------------------------------------------------------------------------------------------------------------------------------------------------------|
|                              | the mental health literacy framework). The attributes are; 1) knowledge of where to seek information; 2) ability to recognize disorders; 3) knowledge of self-treatment; 4) knowledges of risk facts and causes; 5) attitudes that promote recognition or appropriate help-seeking behaviour; and 6) knowledge of professional help available. A cumulative mental health literacy score will be calculated. |
| Help-Seeking Behavior | Knowledge of where to access information and capacity to do so. This section consists of 10 items and measured by ‘agree’ or ‘disagree’. The attributes are openness to seeking treatment for emotional problems and values and need in seeking treatment.                                                                                                                                                   |

---

### 3.7 Study Instruments

The study instruments that will be used in this study is validated questionnaire and a health education intervention.

#### 3.7.1 Questionnaire

The questionnaire will be in dual language (English and *Bahasa Melayu*) where the back-to-back translation will be conducted. All parts of the questionnaire will be self-administrated. The questionnaires consist of the following six sections.

To measure the primary outcome, which is mental health literacy, the questionnaire will be adapted from the Mental Health Literacy Scale (MHLS) (M. O’Connor & Casey, 2015). The internal consistency of MHLS were reported to be  $\alpha=0.8793$ . Whereas, to measure the secondary outcome which is the help-seeking behaviour, the Attitudes Toward Seeking Professional Psychological Help Scale- Short Form (ATSPPH-SF) (Elhai et al., 2008) will be used. The internal consistency of ATSPPH-SF was reported to be  $\alpha=0.77$ . The factor analysis of ASPPH-SF revealed three dimensions includes “openness to seeking professional help”, “value in seeking professional help”, and “preference to cope on one’s own” (Picco et al., 2016).

### **3.7.1.1 Section One- Sociodemographic**

Section one will be sociodemographic factors include age, ethnicity, gender, and household income level.

### **3.7.1.2 Section Two- Mental Health Literacy**

Section two measures mental health literacy using Mental Health Literacy Scale (MHLS) (M. O'Connor & Casey, 2015). This section consists of 35 items. The attributes are the knowledge of where to seek information, ability to recognize disorders, knowledge of self-treatment, knowledges of risk facts and causes, attitudes that promote recognition or appropriate help-seeking behaviour, and knowledge of professional help available. Total score is produced by summing all items. Questions with a 4-point scale are rated 1- very unlikely/unhelpful, 4 – very likely/helpful and for 5-point scale 1 – strongly disagree/definitely unwilling, 5 – strongly agree/definitely willing.

### **3.7.1.3 Section Four Help-Seeking Behaviour**

Section four measures help-seeking behaviour. This section consists of 10 items and measured by 'agree' or 'disagree'. The attributes are openness to seeking treatment for emotional problems and values and need in seeking treatment.

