## **3.8 Quality Control of Study Instruments**

### **3.8.1 Questionnaire**

The content validity for the questionnaire will be performed by three panel of experts which include two Public Health Physicians and one Psychologist. The questionnaire will also be pre-tested, and face validated among 30 young people.

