### **3.8.1.3 Reliability**

Test-retest reliability will also be conducted during the pre-test to ensure it does that answers from the same respondents on the same measurement are correlated. The intra-class correlation coefficient and Cohen's kappa will be measured. Internal consistency reliability will also be conducted during the pre-test to estimate the degree of consistency among the items. Cronbach alpha will be measured and a value of 0.7 and above will be considered as acceptable reliability.

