**Table 3.4 Summary of Statistical Tests**

| Objectives                                                                           | Statistical Tests        |
|---------------------------------------------------------------------------------------------|---------------------------------|
| Sociodemographic                                                                     | Chi-Square                      |
| Baseline Mental Health Literacy and Help-Seeking Behavior                            | Independent t-test              |
| Post Intervention Mental Health Literacy and Help-Seeking (within group difference)  | Paired t-test                   |
| Post Intervention Mental Health Literacy and Help Seeking (between group difference) | Independent t-test              |
| Effect of Health Education Intervention                                              | Generalized Estimating Equation |

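### The ten help-seeking items are recorded only as agree or disagree, which discards strength of attitude for no stated benefit; graded response options would be a cheap improvement if adopted before data collection

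*Combined protocol and SAP*

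**What the plan says.** Section 3.7.1 names the ATSPPH-SF as the measure of the secondary outcome. No other help-seeking measure is planned. On the response format, Section 3.7.1.3 states: "This section consists of 10 items and measured by 'agree' or 'disagree". The help-seeking row of Table 3.2 gives the same format: "This section consists of 10 items and measured by ‘agree’ or ‘disagree". Neither place gives a reason for two options or a rule for scoring the items.

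Section 3.7.1.2 gives the Mental Health Literacy Scale 4-point and 5-point responses and a summed total. Both instruments sit in the same self-administered questionnaire.

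On reliability, Section 3.7.1 states: "The internal consistency of ATSPPH-SF was reported to be" 0.77. It does not say on which response format. Section 3.8.1.3 sets the standard for the pre-test: "Cronbach alpha will be measured and a value of 0.7 and above will be considered as acceptable reliability". Section 3.8.1 gives the pre-test size: "The questionnaire will also be pre-tested, and face validated among 30 young people". No action is stated if alpha falls short.

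For analysis, Table 3.4 lists an "Independent t-test" for between-group help-seeking scores, a paired t-test within groups, and generalized estimating equations (GEE) for the intervention effect. Section 3.10.2 adds Wilcoxon and Mann-Whitney tests for non-normal data.

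**The concern.** An attitude item can change in direction or in strength. With two options, a student who moves from weak to firm agreement gives the same answer twice, and so does one who moves from firm to mild disagreement. The ten items are asked either way, so the coarser format saves almost nothing, and participants already use graded scales a section earlier.

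What is at stake is research question 2. The sample size in Section 3.4.9 rests on the literacy score alone, so help-seeking has no planned power. Section 2.11.5 reports that earlier interventions tended to raise literacy but not help-seeking, so a null result is a real possibility. With a needlessly coarse score, it would be harder to tell absence of effect from insensitivity of the measure. Strength of agreement that is not recorded at the time cannot be recovered later.

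**Working it through.** **Inputs from the documents.** Ten items with two options (3.7.1.3, Table 3.2); alpha 0.77 (3.7.1); threshold 0.7 (3.8.1.3); pre-test of 30 (3.8.1); 44 per arm before and 66 after the allowance for loss (3.4.9). The 0.77 cannot be reproduced, because no item data are given.

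**Assumptions.** One common factor; two-option items treated as cuts of a normal variable; one point per item, summed, since the plan gives no scoring rule; agreement rates from 15% to 90%. Section 3.7.1 mentions a three-dimension factor analysis, so one factor is a simplification.

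**Step 1: sensitivity.** Ten items, loading 0.55, shift of 0.5 SD on the underlying attitude. The four-category comparator has outer cuts 1 SD either side of the agree/disagree cut. Relative efficiency = (d two-option / d four-category)², where d is the standardized group difference.

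| Agreement | Relative efficiency | Loss | Equivalent of 66 per arm |
|---|---|---|---|
| 15% | 0.78 | 22% | 66 × 0.78 = 51.5 |
| 30% | 0.88 | 12% | 66 × 0.88 = 58.1 |
| 50% | 0.90 | 10% | 66 × 0.90 = 59.4 |
| 70% | 0.83 | 17% | 66 × 0.83 = 54.8 |
| 85% | 0.70 | 30% | 66 × 0.70 = 46.2 |

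Recomputing by numerical integration instead of simulation agrees to within 0.01. The loss is larger at high agreement because the assumed shift is upward.

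A separate run, with the loading set so that four-category alpha is 0.77 and an even split, gives d = 0.5009 graded and 0.4714 two-option. The ratio (0.5009/0.4714)² = 1.129 means about 13% more participants for equal power. For that effect, power falls from 65% to 60% at 44 per arm and from 82% to 77% at 66.

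**Step 2: reliability, conditional on 0.77 being graded.** For ten items, alpha = 10r/(1 + 9r), so r = alpha/(10 − 9·alpha).

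- Alpha 0.77: r = 0.77/(10 − 6.93) = 0.251.
- Alpha 0.70: r = 0.70/(10 − 6.30) = 0.189.

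Solve for the latent correlation ρ that gives r = 0.251 on graded items, then convert to two options with φ = (P11 − p²)/(p(1 − p)), where p is the agreement rate and P11 the probability of agreeing with both items. At an even split φ = (2/π)·arcsin(ρ). For four equally used categories, ρ = 0.291, φ = 0.188, and alpha = 1.88/(1 + 1.69) = 0.70.

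| Format assumed behind 0.77 | 50% agree | 70% agree | 90% agree |
|---|---|---|---|
| 3 categories | 0.717 | 0.701 | 0.611 |
| 4 categories | 0.692–0.698 | 0.674–0.681 | 0.579–0.587 |
| 5 categories | 0.683 | 0.665 | 0.568 |
| 2 options | 0.77 as cited; no loss to compute | – | – |

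**Step 3: the pre-test.** With a four-category original and an even split, observed alpha in 30 people falls below 0.7 in about 56% of simulated pre-tests with two options, against 19% with graded responses.

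**The case against.** The strongest reply concerns reliability. A reader might infer that the two-option form will fail the plan's own threshold. The documents do not support that. They do not say which response format produced 0.77. If it was two options, the reliability argument does not apply. If it was three categories, two-option alpha stays at or above 0.70 up to 70% agreement. Even with a four-category original, an even split lands at about 0.70, which is at the threshold and not clearly under it. All of this stands.

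A reader might also infer a ceiling, with most students already agreeing at baseline. Nothing in the documents gives agreement rates. The background sections describe low help-seeking and high stigma, which give no reason to expect 85% agreement on every item. The 30% loss is therefore the worst of the cases examined, not a forecast.

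A third inference is that the plan forces t-tests on a coarse 0-to-10 count. The count itself is inferred, and Section 3.10.2 provides non-parametric alternatives and bases effectiveness on the group-by-time term from GEE.

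The wording may also be loose shorthand for the end labels of a graded scale. That is possible, since Section 3.7.1 says the ATSPPH-SF will be used, but two separate places state the same two options. Anyone building the form from them would offer only those two, so the text needs correcting on either reading.

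Finally, the planned pre-test could reveal low reliability. It is a partial safeguard: it has 30 people and no stated consequence, and alpha does not show the loss of responsiveness.

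**Conclusion.** The point holds as a cheap improvement to the secondary outcome. As written, the form discards strength of attitude with no stated benefit. Under the model above, that costs about 10% to 17% of the effective sample for help-seeking at 50% to 70% agreement, and 22% to 30% at 15% or 85%. These figures rest on one factor, a 0.5 SD latent shift, a four-category comparator and assumed agreement rates. Near an even split the loss of power is modest, about 5 percentage points. The primary outcome is not affected.

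The reliability part is conditional. If, and only if, 0.77 came from a graded version with four or more categories, two-option alpha would be about 0.68 to 0.70 at an even split and lower when answers are lopsided, so it may miss 0.7. The loss of graded information does not depend on that condition.

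**What to change.** Before data collection:

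- In Section 3.7.1.3 and Table 3.2, replace the two options with ordered agreement categories. Check the cited ATSPPH-SF version first. If it is graded, use its response format and scoring, so that the quoted alpha refers to the form in use.
- If the cited version has two options, say so beside the 0.77. A graded form would then be a departure from it, and its reliability would rest on the pre-test.
- State the scoring: align the direction of the items and sum them to one total.
- Use this same version in the 30-person reliability pre-test.

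The cost is one edit to the response options and scoring text, plus seconds more per participant. It adds no items or visits.

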## **3.7.2 Health Education Intervention**

### **3.7.2.1 Designing and Development of Health Education Intervention Program**

The development of the health education module will be going through a few steps. Health intervention module can be developed based on the literature review of previous interventional studies or theory based (Walters et al., 2020; Wang et al., 2017; World Health Organization, 2014a). The development of health education intervention for this study will be based on literature review and the information motivation behavioral theory. The content of the

interventions will be comprised of information on symptoms and causes of mental disorders, available mental health services, pharmacological and non-pharmacological treatment, and self-help strategies. Based on the review, the health education intervention will use active components, to suit the age group (young people) such as video illustrations, quizzes, and vignettes.

The intervention module will then be presented to a panel of experts for content validity. The health education intervention module will also be discussed among the target population (young people) for face validity. This is because it was reported that the involvement of young people during the development of the intervention is recommended. Education intervention with integrating participatory or co-design can increase the effectiveness and sustainability of health education intervention for young people (Bergin et al., 2020; Zorrilla et al., 2019). Figure 3.2 below shows the step of the development of the health education intervention module.

[figure not shown]

**Figure 3.2 Steps of the Development of Health Education Intervention Module**

**Table 3.3 Structure of the Health Education Intervention Program**

| Component and Content of Health Education Material                                                                                                                                                                                                                                                                                      | Intervention Group | Control Group (waitlist) | Strategy Delivery | Method of Delivery  |
|------------------------------------------------------------------------------------------------------------------------------------------------------------------------------------------------------------------------------------------------------------------------------------------------------------------------------------------------|---------------------------|---------------------------------|--------------------------|----------------------------|
| Knowledge 
 
- Epidemiology
 
- Symptoms of anxiety and depression
 
- Risk factors of mental disorder
 
- How to seek mental health information
 
- Self-help intervention
 
- Professional help available
 
 | √                         | √                               | Website                  | Video Information Contact  |
| Motivation 
 
- Ability to recognise specific disorder
 
                                                                                                                                                                                                                            | √                         | √                               | Website                  | Video Information Vignette |
| Behavioural Skills 
 
- Attitude which facilitates recognition and appropriate help-seeking
 
                                                                                                                                                                                       | √                         | √                               | Website                  | Video Information          |

### **3.7.2.2 Implementation of Health Intervention Program**

The health education intervention will be implemented after the baseline assessment was conducted. The health education intervention will be given over a period of 2 weeks with 1 month follow-up. The intervention will be done in four sessions, with two sessions weekly. Each session will take approximately 10 minutes to complete.

The participants will be given a link to the website and an id number. The id number will also be their username to access the website of the health education intervention. This is to ensure that non-participants have no access to the education intervention and as monitoring for completion of the intervention. Weekly email and WhatsApp reminders will also be given to participants to prompt them to complete the session.

### **3.7.2.3 Evaluation of Intervention Program**

The outcome of the health education intervention is mental health literacy. Upon completion of the two weeks intervention period, the impact and outcome of the intervention program will be conducted again, using the same set of questionnaires which consists of the measurements for mental health literacy. The evaluations will then made by comparing the result of the pre-intervention with the result of the post-intervention after the health education program was administered. This will be performed for both the intervention and control groups. The evaluation of the health education process will also be done to control group, to assure or improve the quality of the intervention program.

## **3.8 Quality Control of Study Instruments**

### **3.8.1 Questionnaire**

The content validity for the questionnaire will be performed by three panel of experts which include two Public Health Physicians and one Psychologist. The questionnaire will also be pre-tested, and face validated among 30 young people.

#### **3.8.1.1 Content Validity**

Content Validity of the questionnaire will be done to assess domain clarity, content relevance, and content representativeness by a panel of expert. Content validity index (CVI) will be calculated for each item. Each item will be assessed by an expert based on the content relevance or representativeness through a 4-point Likert scale ranging from 1 (not relevant) to 4 (extremely relevant). I-CVI will be calculated by counting the number of experts who rated the item as 3 or 4 and dividing by the total number of experts (3) (Almanasreh et al., 2019).

### **3.8.1.2 Face Validity**

Pilot testing will be done to assess the feasibility of the questionnaire and testing the measurement instrument (Abu Hassan et al., 2006). A pilot test will be conducted among a similar populations of interest (university students). This is because we need to ensure that the content is culturally acceptable by the target group. Face validity will be conducted to ensure that it measures the construct is supposed to measure.

### **3.8.1.3 Reliability**

Test-retest reliability will also be conducted during the pre-test to ensure it does that answers from the same respondents on the same measurement are correlated. The intra-class correlation coefficient and Cohen's kappa will be measured. Internal consistency reliability will also be conducted during the pre-test to estimate the degree of consistency among the items. Cronbach alpha will be measured and a value of 0.7 and above will be considered as acceptable reliability.

## **3.8.2 Health Intervention Module**

The content validity for the questionnaire will be performed by three panel of experts which include two Public Health Physicians and one Psychologist. The questionnaire will also be pre-tested, and face validated among 30 young people.

### **3.8.2.1 Content Validity**

The health intervention module will be presented to a panel of experts which consists of two public health physician and one psychologist. All items which include the theory of planned behaviour-based health education module, videos, content will be presented for the panel to review extensively. All comments and feedback will be taken and the amendment will be done accordingly.

